On the other hand, the frequent user of CR showed stronger downregulation of amygdala activation to negative emotion stimuli (Kanske et al., 2012), and CR in healthy individuals can attenuate the excitatory connectivity from the dlPFC to the inferior frontal gyrus (IFG) and increase the inhibitory connectivity from the IFG to the dlPFC, which supports the selection of appropriate alternative CR strategies (reinterpretations) in the IFG, and afterward, inhibition of original interpretations maintained and monitored in the dlPFC (Morawetz et al., 2016). Neurofeedback-guided CR training targeting the left vlPFC improved the frequency of CR strategy use (indexed with ERQ) as well as depression symptoms (Keller et al., 2021). Therefore, CR training may enhance CR ability by changing the functional activity/connectivity pattern of prefrontal-amygdala circuits, which then alleviates cognitive biases and thus depressive symptoms.

Researchers suggested that specific measures using lab-based tasks may be more sensitive to detect training effects (Cohen and Ochsner, 2018). Therefore, in this study, we will combine the RIT, CR training, and fMRI, as well as self-report measures (cognitive/emotion/symptoms) to address the following aims: (1) to examine whether the CR ability (reappraisal inventiveness) of the population with cognitive vulnerability to depression is abnormal; (2) to test the hypothesis that CR training alleviates depressive symptoms through the mediators of cognitive bias (e.g., interpretation bias and/or rumination bias); (3) to investigate the neural substrates (structural/functional) of prefrontal–amygdala circuits through which CR training improves the ability to generate a CR strategy; and (4) to examine the short- and/or long-term effects of CR training on reducing depression symptoms in cognitively vulnerable individuals immediately after intervention and/or 6 months to provide theoretical and practical evidence for early intervention in these populations. We postulate that CR training improves CR ability (RIT) by changing the brain activity/function connectivity of the prefrontal-amygdala circuits, thereby reducing negative cognitive biases (NCPBQ-NIB, NCPBQ-NRB, and CSQ) and improving depression symptoms (CESD) (Figure 1).

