Randomization to treatment will be completed with a computer-generated list of random numbers, and each participant will be randomly assigned to either the intervention group or the control group with a 1:1 allocation and double-blinded. The randomization will minimize group differences in demographic factors and instrument scores (Pocock and Simon, 1975).

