### Statistical analysis

#### Behavioral and self-report data

##### Intervention effect analysis

A 3 (group: CR = cognitively vulnerable intervention subgroup; WC = cognitively vulnerable waiting-list control subgroup; NC = normal control group) × 3 (time point: T_0_ = pretraining, T_1_ = post-training, T_2_ = 6-month follow-up) mixed design will be adopted. Using the HLM analysis, as well as mediating/modulating effect analyses, we will investigate (1) hypothesis 1, whether the changes in negative cognitive biases and depressive symptoms across time 1 and time 2 differ significantly among groups and (2) hypothesis 2, whether the changes in negative cognitive bias (negative interpretation bias and/or negative rumination bias) pre- and post-training could predict depression symptoms at T_1_ and/or T_2_.

To test hypothesis 1, we will conduct an HLM analysis with time (0 = pretraining; 1 = post-training), group (0 = CR; 1 = WC; 2 = NC), and the interaction between time and group as predictor variables and the with CESD score as the outcome variable. To test hypothesis 2, we will conduct mediating/modulating effect analyses among CR ability (RIT) and tendency (ERQ), negative cognitive bias (NCPBQ), cognitive vulnerability (CSQ), and depressive symptoms (CESD) at T_1_ and/or T_2_. The HLM and mediating/modulating effect analyses will be conducted in SPSS (Statistical Product and Service Solutions) software version 22.0 (SPSS, Inc., Chicago, IL, United States) combined with the PROCESS Macro (Hayes, 2012).

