(3) Functional connectivity analysis: Taking the amygdala as the seed point and the average time series within the seed point as the reference time series, we will perform “one point to multipoint” linear correlation analysis with the time series of each ROI. Using the average signals of head movement, the white matter, the cerebrospinal fluid, and the whole brain as covariates and using the prefrontal-amygdala FCs as predictors of depressive symptom scores, we will use between-group *t*-tests, combined with correlation analyses and path analyses, to examine (1) whether the FCs between the prefrontal subregions (dlPFC/vlPFC/dmPFC/vmPFC) and the amygdala before and after CR training differ significantly and (2) if the prefrontal-amygdala FCs do differ significantly, whether the FCs could predict depressive symptoms (T_1_ and T_2_). The FCs between ROIs, cognitive bias (CSQ/NCPBQ), CR ability (RIT), and tendency (ERQ) will then be entered into path analyses to verify the cognitive bias model of CR training.

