This study also proposes a novel cognitive bias model of CR training (CR training→cognitive bias↓→cognitive vulnerability to depression↓), which hypothesizes that CR training may improve CR ability (effectiveness and incentives) and reduce cognitive bias (negative interpretation bias and/or negative rumination bias), which then alleviates the depressive symptoms. We adopt a process-based approach, which emphasizes the primary cognitive process underlying intervention (Forgeard et al., 2011) and assesses the effectiveness of the training using behavioral (RIT), cognitive (CSQ/NCPBQ), and clinical (CESD) assessments, along with measures of task-related brain activity/FCs before and after the training. This approach may provide proof-of-concept evidence for the cognitive bias model of CR training. In summary, the following scientific questions are expected to be answered: whether CR training will change prefrontal–amygdala FCs in the short term and the structure of the regions among the circuits in the long term (6 months later). The current study is promising to provide a novel approach to the intervention of depression vulnerability and insights into the underlying neurocognitive mechanism.

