## Limitations

First, we include the process measures of cognitive bias (negative interpretation bias and/or negative rumination bias) to evaluate the intervention effects, which should be interpreted as exploratory. More solid progress will depend on a systematic examination of the neural network mechanism involved in CR training effectiveness. The neural signature of the cognitive control and emotion regulation network during CR, such as global metrics and topological characteristics (Pan et al., 2018), is needed. However, connectome-based predictive modeling of distributed neural networks during CR has not revealed a meaningful whole-brain signature of CR tendency (Pan et al., 2018; Burr et al., 2020). Therefore, more evidence is needed to explore the neural network mechanism of CR training, which may provide more perspectives on the neural and cognitive targets of CR training.

Second, evidence of both clinical effectiveness and cost effectiveness of CR training is necessary for future studies to test the feasibility of CR training in primary care, as well as in clinical settings for vulnerable individuals with depression, and generalize CR training to those populations that may benefit from training. Therefore, various context-specific CR training programs should be forged into well-specified protocols that could be tested in randomized controlled trials to provide such evidence. Furthermore, further studies comparing CR training with other components of CBT as well as its whole package are warranted to assess its cost-effectiveness.

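### The mediation and path models do not name the randomised arm, so as written they do not estimate an effect of training through cognitive bias

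*Protocol article*

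**What the plan says.** The Introduction states aim 2 as a causal claim: "to test the hypothesis that CR training alleviates depressive symptoms through the mediators of cognitive bias", with interpretation and rumination bias as the examples. The Discussion draws the same chain with training at its start: "novel cognitive bias model of CR training (CR training→cognitive bias↓→cognitive vulnerability to depression" (downward arrow).

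The analysis is given under Statistical analysis, Intervention effect analysis. Hypothesis 2 asks whether changes in bias "pre- and post-training could predict depression symptoms at T_1_ and/or T_2". The models to test it are "mediating/modulating effect analyses among CR ability (RIT) and tendency (ERQ), negative cognitive bias (NCPBQ), cognitive vulnerability (CSQ), and depressive symptoms (CESD"), fitted in SPSS with the PROCESS macro.

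Group is a named predictor only in the hypothesis 1 model: "group (0 = CR; 1 = WC; 2 = NC), and the interaction between time and group as predictor variables", with CESD as the one outcome specified. Hypothesis 1 also mentions changes in bias, but no model with bias as outcome is written out.

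Under Neuroimaging data, Data analysis, item (3), the model meant to verify the cognitive bias account of training is described as follows: "The FCs between ROIs, cognitive bias (CSQ/NCPBQ), CR ability (RIT), and tendency (ERQ) will then be entered into path analyses".

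Allocation of the vulnerable participants is randomised: "randomly assigned to either the intervention group or the control group with a 1:1 allocation". The Limitations section says the bias process measures are included "to evaluate the intervention effects, which should be interpreted as exploratory".

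**The concern.** A test of whether training works through bias needs two links: arm to bias, and bias to symptoms given arm. The lists for hypothesis 2 and for the path analyses hold candidate mediators and the symptom outcome, but not the arm. Without it there is no training effect to divide into direct and indirect parts. People who generate more reappraisals may have less negative bias and fewer symptoms whether or not anyone is trained. A significant path from RIT through bias to CESD could then be reported as support for aim 2 although it says nothing about training.

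Timing is a lesser matter. The plan allows bias change over T0–T1 to be related to CESD at T1. The T1 bias score and the outcome are then self-reports from the same assessment point, and shared mood can link them.

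**Working it through.** **1. Aim and models side by side**

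| Place | Content | Arm named? |
|---|---|---|
| Introduction, aim 2 | training → bias → symptoms | yes |
| Discussion, conceptual model | training → bias → vulnerability | yes |
| Hypothesis 1 model | time, group, time × group → CESD | yes, but bias is not the outcome |
| Hypothesis 2 mediation | RIT, ERQ, NCPBQ, CSQ, CESD | no |
| Imaging path analyses | FCs, CSQ/NCPBQ, RIT, ERQ | no |

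No model that is written out contains arm, bias and symptoms together.

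**2. Size used.** The plan gives no figure for mediation. Its sample-size statement supplies 75 per group, 150 in all. That figure reproduces: at d = 0.39 (printed as 0.0.39), with two-sided 5% assumed, power is 66–67% against 65% stated, and 150 / (1 − 0.20) = 187.5, rounded up to 188. It does not bear on this point beyond fixing N = 150.

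**3. Level scores, training does nothing.** Models: bias = i₁ + a·X + e₁; CESD = i₂ + c′·X + b·bias + e₂. The indirect path counts as significant when a and b both have p < 0.05. The RIT–bias correlation is −r, bias–CESD is r, and RIT–CESD is −r². There were 4,000 runs.

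| r | X = RIT | X = arm | bias–CESD alone |
|---|---|---|---|
| 0.2 | 45% | 3.4% | 67% |
| 0.3 | 91% | 5.0% | 96% |
| 0.395 | 99.7% | 4.9% | 99.9% |
| 0.5 | 100% | 4.8% | 100% |

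Hand check at r = 0.2: each link is found in about 67.2% of runs, and 0.672 × 0.672 = 0.451. With arm as X the first link is a chance finding: 0.05 × 0.672 = 0.034. Only 0.395 comes from the article (NCPBQ against the Beck scale, not CESD); the other correlations are assumptions.

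**4. Change in bias as mediator.** Write bias at time t as T + Sₜ + eₜ (stable trait, state, error). The change is (S₁ − S₀) + (e₁ − e₀), so T drops out. With no training effect, N = 150, trait correlations −0.3 (RIT with bias and with CESD) and 0.5 (bias with CESD), trait share of variance 0.6 and shared-mood share 0, 0.3 or 0.5 (1,000 runs):

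- T1 level scores: false path in 54–61%.
- Bias change, CESD at T1: 0–4%.
- Bias change, CESD at T2: at most 0.3%.
- Bias change, CESD at T1, RIT also sharing the visit mood (separate run): 6–36%.

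Across the settings tried, arm as X gave at most about 6%.

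**5. Timing once arm is in the model.** Assumed: 75 per arm, arm effects of −0.5 on bias and −0.39 on CESD, no effect of bias on symptoms, retest correlation 0.6, trait correlation 0.4, shared-mood share 0.3 / 0.5, 2,000 runs. False mediation:

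| Model | 0.3 | 0.5 |
|---|---|---|
| Bias change, CESD at T1 | 33% | 73% |
| T0-adjusted T1 bias, CESD at T1 | 95% | 97% |
| T0-adjusted T1 bias, CESD at T2 | 32% | 54% |
| As the line above, plus T1 CESD | 4.4% | 5.7% |

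The last line has a price. Where mediation is real and has acted by T1, adding T1 CESD cut power from 83% to 50% (b = 0.3) and from 97% to 76% (b = 0.5).

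**The case against.** - **The lists may be constructs, not full models.** The hypothesis 2 text fixes no independent variable, mediator or outcome. It sits under an intervention-effect heading within a three-group, three-time design, and one sentence applies mediation analysis to both hypotheses. The path-analysis list also omits CESD, so it is not exhaustive. This stands in part: arm may be intended. But nothing makes it the independent variable of an indirect effect. The mention of modulating effects and the between-group t-tests in the imaging section do not do so either. A list that names every other variable but not the exposure in the aim is more than condensed detail.
- **The stated mediator is a change score.** This stands. A reader might infer from the level-score figures that the mechanism would nearly always be confirmed falsely. The plan does not support that, because differencing removes stable traits and the rate falls to 0–4% unless RIT shares the visit mood.
- **T2 is already allowed.** This stands. The same-visit problem is an option in the plan, not a requirement. T2 does not, however, bring the arm into the model.
- **The bias measures are labelled exploratory, and the Conclusion promises only initial evidence.** This lowers the weight. It does not make a model without arm informative about training, and the Introduction still speaks of testing a hypothesis.

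**Conclusion.** The point holds as a mismatch between aim and model. The listed mediation and path models do not estimate an effect of training through bias. The text is enough to show this; the simulations only indicate how misleading the result could be.

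That size depends on an analysis choice. With level scores and no training effect, roughly half to nearly all trials could show a significant RIT–bias–CESD path. With bias change as mediator, few would, unless the measures share mood at the visit. All these rates rest on assumed correlations.

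Two stronger readings fail. Shared mood at T1 does not invalidate the plan, since T2 is available. Nor do the simulations show the mechanism being confirmed with both training and bias inert under the plan's change-score model: the 33–73% results assume that training does lower both bias and symptoms.

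The primary comparison of CESD between arms is unaffected.

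**What to change.** 1. Fit the mediation in randomised participants only, CR versus WC. Leave out the normal controls, who are not randomised and are selected from the opposite end of the CSQ distribution.
2. Set arm as the independent variable, T1 NIB or NRB adjusted for its T0 value as mediator, and CESD adjusted for T0 CESD as outcome.
3. Make T2 CESD the main outcome and label the T1–T1 model descriptive.
4. Enter arm at the head of the imaging path model.
5. State that mediation of training will not be claimed from models without arm.
6. Add T1 CESD as a covariate in a sensitivity analysis only. It is measured after randomisation, removes benefit already reached by T1 and lowers power. Because the model without it is open to confounding of bias and symptoms (32–54% above), report both and read any disagreement cautiously.

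**Cost:** a re-specification in the software already named, with no new data. The T2 model uses T2 completers and has less power. The bias-to-CESD link stays non-randomised, so it rests on no unmeasured confounding and remains exploratory. The article does not say whether the waiting-list arm is trained before T2; check this before relying on the T2 contrast.

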#### Neuroimaging data

##### Data preprocessing

Structural data preprocessing: The raw data will be analyzed with the CAT (Computational Anatomy Toolbox) 12 toolbox.^1^ (1) Segmentation: The T1-weighted image for each pair of participants will be normalized to a template MNI space using DARTEL normalization and segmented into gray matter (GM), white matter (WM), and cerebrospinal fluid (CSF). (2) Check data quality: The written data will be checked to exclude those with artifacts or orientation errors. (3) The GM images will be smoothed using a Gaussian kernel of 8 mm full-width half-height (FWHM) and then entered into the statistical analysis.

Functional data preprocessing: The raw data will be formatted using MRIcro software^2^ and the data will be preprocessed using the internationally accepted software Statistical Parametric Mapping 12 (SPM12) (Wellcome Trust Center for Neuroimaging.^3^ (1) Functional data for the first 10 repetition times (TRs) will be excluded to eliminate the effects of subject maladaptation and longitudinal magnetization relaxation not reaching the steady state. (2) Head movement correction: This will be performed to reduce the interference of noise signals caused by the subject’s head movement during the scanning process, and data with head motion exceeding 1.5 mm or a rotation angle exceeding 1.5° will be excluded. (3) Time point correction: This will be performed to standardize the images collected at different time points to the same time point based on the time modulation effect of the hemodynamic function on each functional image. (4) Alignment: To address the differences in the anatomical structure of different individuals, each subject’s functional images and templates will be aligned so that the individual’s brain is aligned to the standard Montreal Neurological Institute (MNI) space for functional localization of activation zones. (5) Gaussian smoothing: The full width at half maximum value will be set to 8 mm to improve the signal-to-noise ratio of images.

##### Data analysis

(1) Analysis of the morphological characteristics of brain structure: Voxel-based morphometry (VBM) will be adopted to calculate the concentration and volume of each voxel in different brain tissues (gray matter, white matter, and cerebrospinal fluid) using templates for the whole brain and different brain tissues created based on 3D data, and the volumes of ROIs will be compared between different groups to examine (1) whether the volumes of ROIs before and after CR training differ significantly and (2) if the volumes of ROIs differ significantly, whether the changes in the volumes of the ROIs can predict depressive symptoms immediately after training (T_1_) or 6 months later (T_2_).

(2) Region of interest analysis: The anatomical localization of functional images will be determined with reference to the anatomical maps of the brain in Talairach coordinates and based on the opinions of experienced neuroimagers. Using MARSbar software, the prefrontal subregions (dlPFC/dmPFC/vlPFC/vmPFC) and the amygdala will be extracted as BOLD signals of ROIs by subtraction between the baseline and CR (±) conditions. The data will then be exported to SPSS for statistical processing, in which the activation of the region of interest will be used as a predictor of depressive symptom scores to investigate (1) whether the activation levels of regions of interest (prefrontal lobe and the amygdala and its subregions) before and after CR training differ significantly and (2) if the activation levels do differ significantly, whether the changes in the activation levels of the regions of interest can predict depressive symptoms (T_1_ and T_2_).

(3) Functional connectivity analysis: Taking the amygdala as the seed point and the average time series within the seed point as the reference time series, we will perform “one point to multipoint” linear correlation analysis with the time series of each ROI. Using the average signals of head movement, the white matter, the cerebrospinal fluid, and the whole brain as covariates and using the prefrontal-amygdala FCs as predictors of depressive symptom scores, we will use between-group *t*-tests, combined with correlation analyses and path analyses, to examine (1) whether the FCs between the prefrontal subregions (dlPFC/vlPFC/dmPFC/vmPFC) and the amygdala before and after CR training differ significantly and (2) if the prefrontal-amygdala FCs do differ significantly, whether the FCs could predict depressive symptoms (T_1_ and T_2_). The FCs between ROIs, cognitive bias (CSQ/NCPBQ), CR ability (RIT), and tendency (ERQ) will then be entered into path analyses to verify the cognitive bias model of CR training.

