### Brain structure and functional imaging

Brain structure and functional imaging data will be collected on a Siemens 3.0T scanner from the affiliated hospital of the university. During the scan, each participant will be in a supine position, with foam under the head to minimize head movement, and will be wearing headphones to reduce noise interference. A standard orthogonal single-channel head coil will be used. Conventional T1WI and T2WI imaging, echo-planar imaging (EPI), and whole-brain 3D magnetization-prepared rapid gradient-echo (MPRAGE) imaging will be conducted for each subject by a radiologist. The experimental stimulus will be presented by connecting a liquid-crystal display (LCD) screen outside the scanning channel to the E-prime stimulus presentation and the response recording system, and each participant will view the presentation through a reflective mirror attached to the head coil. During the experiment, the participant will use a joystick to enter their ratings while the system automatically records the participant’s response to the CR tasks.

The scanning sequence will be as follows: **(1)** The axial T1-FLAIR sequence, parallel to the anterior-posterior joint line; pulse repetition time/echo time (TR/TE) = 500 ms/14 ms; slice thickness = 4 mm; field of view (FOV) = 240 mm × 240 mm; and matrix = 256 × 160; **(2)** sagittal T2-FLAIR will be scanned at the same location using gradient-echo echo-planar imaging (EPI) with the following parameters: TR/TE = 3,000 ms/40 ms; FOV = 240 mm × 240 mm; matrix = 128 × 128; 30 consecutive images at each time point; and slice thickness = 4 mm; if no abnormality is observed in plain scans, resting-state scans will be performed; **(3)** a total of 176 consecutive slices in the sagittal position will be acquired to cover the entire brain through an MPRAGE sequence for subsequent 3D reconstruction and spatial alignment with the following parameters: TR/TE = 1,970 ms/3.93 ms; flip angle = 15°; slice thickness = 1.70 mm; interval = 0.85 mm; FOV = 250 mm × 250 mm; and matrix = 448 × 512; and **(4)** task-state blood-oxygen-level-dependent (BOLD) functional images will be acquired using the EPI sequence, with the same position as that for anatomical images and the following parameters: TR/TE = 2,000 ms/30 ms; number of slices = 36; slice spacing = 33; FOV = 240 mm × 240 mm; and matrix = 64 × 64.

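### Images are normalised to MNI space, but functional regions of interest are localised by Talairach maps and expert opinion, with no link between the spaces and no fixed boundaries

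*Protocol article*

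**What the plan says.** Two parts of the neuroimaging section of the protocol article bear on where the regional signals come from.

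- **Data preprocessing.** Structural images are to be "normalized to a template MNI space using DARTEL normalization". Functional images are aligned to templates so that "the individual’s brain is aligned to the standard Montreal Neurological Institute (MNI) space for functional localization of activation zones".
- **Data analysis, item (2), region of interest analysis.** Anatomical localisation of the functional images is to be determined "with reference to the anatomical maps of the brain in Talairach coordinates and based on the opinions of experienced neuroimagers". The next sentence gives the extraction: "Using MARSbar software, the prefrontal subregions (dlPFC/dmPFC/vlPFC/vmPFC) and the amygdala will be extracted as BOLD signals of ROIs".

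The amygdala then has a second use, in item (3), functional connectivity: "Taking the amygdala as the seed point and the average time series within the seed point as the reference time series". The resulting connectivities are tested, used to predict depressive symptoms, and entered into path analyses intended to verify the cognitive bias model.

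The regions-of-interest paragraph under Brain structure and functional imaging names four prefrontal subregions and the amygdala. It gives no mask, coordinate, radius or boundary.

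**The concern.** MNI and Talairach are different coordinate systems. The article chooses MNI for localisation in preprocessing and Talairach for localisation in analysis, and does not say how one is carried to the other. A coordinate taken from a Talairach map and used as it stands on an MNI image need not fall on the structure intended.

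The second criterion, the opinion of neuroimagers, has no rule attached. The article does not say what they decide, whether they decide it once for all participants or image by image, whether they do so before activation maps exist, or whether they know group and time point.

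The third aim rests on these signals. Item (2) tests whether activation changes with training and, if it does, whether the change predicts depressive symptoms. Item (3) builds every connectivity estimate on one seed. A badly placed amygdala region would therefore affect its own activation result, all prefrontal–amygdala connectivities and the path model. Any subjectivity in defining regions at the first step would carry into the prediction step.

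**Working it through.** The plan states no figure on this point, so there is none to reproduce. The check compares what each section says about location.

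| Step | Reference stated | Section |
|---|---|---|
| Structural normalisation | MNI, by DARTEL | Data preprocessing |
| Functional normalisation | MNI, for localisation | Data preprocessing |
| Anatomical localisation of functional images | Talairach maps plus expert opinion | Data analysis, item (2) |
| Signal extraction | MARSbar; source of masks not stated | Data analysis, item (2) |
| Connectivity seed | Amygdala; boundary not stated | Data analysis, item (3) |

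**Step 1: is there a link between rows 2 and 3?** None appears in either neuroimaging subsection or in the regions-of-interest paragraph. Localisation is assigned to two systems.

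**Step 2: does row 3 govern row 4?** The extraction sentence follows the Talairach sentence directly, in the paragraph headed region of interest analysis. It is reasonable to read the localisation as defining the extracted regions, but the article does not say so outright.

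**Step 3: the scale on which displacement matters.** The BOLD acquisition has "FOV = 240 mm × 240 mm; and matrix = 64 × 64", so the in-plane voxel is 240 / 64 = 3.75 mm. A shift of a few millimetres is about one voxel.

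**Step 4: illustration only.** Neither the offset d nor the region size is in the documents, and the article mentions no spherical regions. For two equal spheres of assumed radius r with centres d apart, the shared fraction of volume is

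1 − 3d/(4r) + d³/(16r³).

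For r = 6 mm and d = 4 mm: 1 − 12/24 + 64/3456 = 0.52.

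| Assumed r | d = 0 | 2 mm | 4 mm | 6 mm | 8 mm |
|---|---|---|---|---|---|
| 6 mm | 100% | 75% | 52% | 31% | 15% |
| 8 mm | 100% | 81% | 63% | 46% | 31% |
| 10 mm | 100% | 85% | 70% | 56% | 43% |

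The d = 0 column applies, approximately, if a correct transform or MNI masks are used. The table shows only that a given shift costs a small region more than a large one. It does not show the share of signal retained, because the functional data are smoothed ("The full width at half maximum value will be set to 8 mm to improve the signal-to-noise ratio of images") and smoothing spreads signal across sharp region edges. It does not estimate what will happen in this trial.

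**Step 5: direction.** A fixed offset shared by all groups and time points would sample the wrong or a mixed tissue equally everywhere. It would dilute or mislabel a regional effect, but would not by itself create a difference between groups or between visits.

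**The case against.** The strongest defence is that a missing conversion is an omission, and a journal article may leave transforms, mask files and region sizes to a fuller document. This stands as far as it goes: the lack of a stated transform would not be a finding on its own. But the article does more than omit. It commits to a localisation rule, Talairach maps plus opinion, beside a preprocessing step that assigns localisation to MNI. A later plan that fixed MNI masks would have to replace that sentence, not merely add to it.

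It is also fair to say that the sentence could describe labelling of activation and not construction of masks. That reading is open, although the sentence's place in the region-of-interest paragraph points the other way.

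A reader might infer three stronger things that the documents do not support:

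- **The signals will come from the wrong place.** This requires Talairach coordinates to be used unconverted, which the article nowhere says.
- **Boundaries will be drawn around observed activation.** The article does not say that the neuroimagers see activation results or group labels, or that they redraw anything. The regions are named in advance, with a rationale in the Introduction. The plan does not exclude placement after the fact, but it does not prescribe it.
- **The trial's main result is compromised.** The CESD and the behavioural models do not use these signals.

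**Conclusion.** The point holds as a badly fixed method. The stated localisation conflicts with the stated normalisation space, and it rests on unconstrained opinion for the regions behind the third aim, including the only connectivity seed.

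The size of any displacement cannot be derived from the documents; it ranges from about zero upward, depending on whether coordinates are converted. If they are not, the likely harm is dilution or mislabelling of regional effects, worst for the amygdala. Bias between groups or visits would need opinion-based placement informed by group, visit or activation. That is possible under the text but not stated in it.

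The conclusion assumes that the localisation sentence governs the extracted regions. It is limited to the neuroimaging activation, connectivity and path analyses.

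**What to change.** Replace the Talairach-and-opinion sentence in item (2) with a rule on these lines: all region masks, including the amygdala seed, are defined in MNI space from one named atlas before the data are seen, and the same masks are applied in MARSbar to every participant at every time point. If neuroimagers review the images, limit their role to anatomical quality control, blind to group and time point, with no redrawing of boundaries.

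This costs a short change to the text and one fixed mask set, with the same images and software. The ethics statement says that no participant had been recruited at submission, so at that date the change could have been made before any data existed. The downside is less tailoring of regions to individual anatomy.
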